#### ARM B:

Patients will receive treating physician's choice of traditional systemic chemotherapy for their malignancy, defined by National Comprehensive Cancer Network (NCCN) guidelines and/or tumor board recommendation(s). If there is no standard of care treatment, the treating physician may select a regimen based upon published reports, series, and/or clinical trials

A treatment regimen will be administered for approximately 8 weeks as dictated by recommendations for approved anti-cancer agents or as dictated by clinical trials. Disease-appropriate imaging (i.e., PET-CT vs. CT vs. MR imaging) will be performed at approximately week 8 according to standard of care or required clinical trial practices.

### Study Group 3

#### ARM A:

A treatment regimen will be administered for approximately 8 weeks as dictated by recommendations for approved anti-cancer agents or as dictated by clinical trials. Disease-appropriate imaging (i.e., PET-CT vs. CT vs. MR imaging) will be performed at approximately week 8 according to standard of care or required clinical trial practices. Objective tumor response will be determined according to RECIST v1.1 and this First Response assessment will guide subsequent treatment according to the following:

2. Patients demonstrating a PR or CR per RECIST 1.1 will continue treatment until
  - a complete response persists for at least six months
  - the tumor becomes resectable
  - their tumor response declines to SD or PD
  - they experience unacceptable toxicity.

## ARM B:

Patients will receive treating physician's choice of traditional systemic chemotherapy for their malignancy, defined by National Comprehensive Cancer Network (NCCN) guidelines and/or tumor board recommendation(s). If there is no standard of care treatment, the treating physician may select a regimen based upon published reports, series, and/or clinical trials.

A treatment regimen will be administered for approximately 8 weeks as dictated by recommendations for approved anti-cancer agents or as dictated by clinical trials. Disease-appropriate imaging (i.e., PET-CT vs. CT vs. MR imaging) will be performed at approximately week 8 according to standard of care or required clinical trial practices.

### **Dosing Delays/Dose Modifications**

Dose modifications will be determined by the treating physician appropriate for the particular agent administered. Investigational agents administered on clinical trials will have specific dose modifications provided in that trial. FDA approved drugs will be dosed in accordance with the package insert. Toxicities, dose reductions and monitoring will follow protocol for investigational drugs and package inserts for approved drugs. All toxicities grade 3 and above will be tabulated for FDA approved drugs. For investigational drugs on protocol, toxicities will be tabulated per protocol.

### **Permitted concomitant therapy**

Supportive care and medical management drugs/treatments are allowed as deemed appropriate by the treating medical oncologist and consistent with treatment guidelines and clinical trials.

### **Prohibited concomitant therapy**

Investigational-targeted therapies may be used while the patient is on the study if they are the appropriate matched therapy for the patient's disease. If additional un-matched anti-cancer agents are administered in combination with matched therapy, then the patient will no longer be considered to be on matched therapy unless the patient already received that unmatched therapy and did not achieve a PR or CR.

### **Other Modalities or Procedures**

Modalities (e.g., surgery, radiotherapy) or procedures (e.g., tumor biopsy by a surgeon, interventional radiologist/gastroenterologist/pulmonologist) will be standard of care. No additional modalities or procedures will be offered within the protocol.

### **Duration of Follow Up**

Patients will be followed every 3 months ( $\pm 1$  month) until death for survival contacts.

### **Patient Replacement**

Patients may be replaced if they have withdrawn from the study prior to having their tumor profiled in order to obtain 1150 evaluable patients with FoundationOne™ analyses.

## **4.0 STUDY PROCEDURES**

---

### **Screening/Baseline Procedures**

Assessments performed exclusively to determine eligibility for this study will be done only after obtaining informed consent. Assessments performed for clinical indications (not exclusively to determine study eligibility) may be used for baseline values even if the studies were done before informed consent was obtained.

### **Informed Consent**

Subjects will be asked to provide written consent using an IRB-approved consent form. The investigator or study coordinator will describe the study, including detailed information about risks, benefits, and voluntary nature of the study, to potential subjects. Subjects will be given ample time to read the consent form at the same visit or may take it with them to read at another time. Potential study subjects will be given the opportunity to ask any questions they may have about the study, including its risks and benefits, or about the consent form itself before signing the consent form. As this research is subject to HIPAA privacy rule provisions, participants will also be requested to sign a separate authorization for the use of protected health information (i.e., HIPAA form specific to the research study).

The investigator or study coordinator will obtain informed consent in a language understood by the prospective participant or their legally authorized representative, using certified translations of study documents and qualified translators, where applicable.

Patients who fulfill the eligibility criteria will be offered further participation in this study. Only patients who have consented and provided HIPAA authorization will have identifiers or linked information (e.g., patients initials, study numbers, etc.) recorded on the Screening/Enrollment Log.

### **Medical history**

Complete medical, surgical and oncology history as well as history of infections are obtained at screening.

### **Demographics**

Demographic profile will include date of birth, gender, race, and ethnicity.

### **Review subject eligibility criteria**

Review of eligibility criteria to ensure subject qualification for study entry.

### **Performance status**

ECOG performance status evaluated prior to study entry.

### **New York Heart Association Classification**

Classification evaluated prior to study entry.

### **Hematology**

As dictated by standard of care or a clinical trial.

### **Serum chemistries**

As dictated by standard of care or a clinical trial, including pregnancy test for women of child bearing potential.

### **Assessments for an individual protocol or drug**

Assessments specific for an individual treatment protocol or drug will be performed as indicated by that protocol. Examples may include additional blood work and an echocardiogram. Patients must meet eligibility criteria for enrollment on any other given trial.

### **Tumor assessment**

Tumor imaging (or clinical exam when applicable) will be performed as part of standard of care. Imaging based evaluation should always be done rather than clinical examination unless the lesion(s) being followed cannot be imaged but are assessable by clinical exam. The same method of assessment and the same technique should be used to characterize each identified and reported lesion at baseline and during follow-up.

Patients will be considered evaluable for the study if they had their baseline scan within 30 days of the start of therapy. Tumor measurements will be assessed according to RECIST v1.1 (see Appendix A).

In addition, biochemical markers (tumor markers) may be considered as a secondary method for assessing tumor response.

### **Tumor markers (for diseases included, but not limited to)**

|                                                 |              |
|-------------------------------------------------|--------------|
| Ampullary carcinoma                             | CEA          |
| Appendiceal cancer                              | CEA          |
| Breast cancer                                   | CA15-3       |
| Colorectal cancer (CRC)                         | CEA          |
| Esophageal adenocarcinoma                       | CEA          |
| Extrahepatic cholangiocarcinoma (EHCC)          | CEA, CA-19-9 |
| Gallbladder cancer (GBCA)                       | CEA, CA-19-9 |
| Gastric adenocarcinoma                          | CEA          |
| Hepatocellular carcinoma (HCC)                  | AFP, DCP     |
| Intrahepatic cholangiocarcinoma (IHCC)          | CEA, CA-19-9 |
| Ovarian cancer                                  | CA-125       |
| Pancreatic ductal adenocarcinoma (PDAC)         | CA-19-9      |
| Prostate cancer                                 | PSA          |
| Small bowel adenocarcinoma (including duodenal) | CEA          |

### **Molecular Profiling**

A sample of the subject's blood will be collected or the subject's tumor will be obtained via biopsy, surgical resection, or fine needle aspiration during screening and prior to study treatment. For new tumor samples procured at UCSD, tissue will be placed in formalin and sent to the UCSD Department of Pathology for clinical care. For new tumor samples procured at Avera McKennan, tissue will be placed in formalin and sent to the Avera McKennan Department of Pathology for clinical care. The tissue will be formalin-fixed paraffin-embedded (FFPE). All clinical diagnoses will be performed. For subject's tumor samples previously biopsied at UCSD or outside institutions, pathological re-examination and diagnosis confirmation by the UCSD Department of Pathology faculty will be performed at the discretion of the treating physician. For Avera McKennan's subject's tumor samples previously biopsied at Avera McKennan or outside institutions, pathological re-examination and diagnosis confirmation by the Avera McKennan Department of Pathology faculty will be performed at the discretion of the treating physician. For tumor samples procured from outside institutions, a slide case request will be performed prior to receipt of tissue. A pathologist will then review the FFPE blocks as described below. Subsequently, 8-10 unstained FFPE slides plus 1 H&E slide as needed will be sent to Foundation Medicine for FoundationOne™ analysis.

Alternatively, for tumor samples (FFPE slides or blocks) procured from outside institutions where pathological re-review is not deemed to be clinically necessary according to the treating physician, FFPE blocks or about 8-10 unstained FFPE slides plus 1 H&E slide as needed will be directly sent to Foundation Medicine for FoundationOne™ analysis.

Tissue/blood samples will be shipped ambient by priority overnight FedEx to the following address:

[name]  
Foundation Medicine, Inc.  
[name]  
[name]

No additional tissue/blood will be retained for this protocol.

[name], Director of Anatomic Pathology, or her designee, will be responsible for reviewing and approving requests for clinical specimen to be sent to Foundation Medicine, a CLIA certified laboratory. Any data obtained from the use of clinical specimen will be the property of UCSD for publication and any licensing agreement will be strictly adhered to. Following patient consent and HIPAA compliance, annotated clinical information will be sent to Foundation Medicine. There will be secure storage of linking data kept in the form of paper and electronic files. These will be stored in the Clinical Trials Office. Results of genomic testing will also be uploaded to the patient's electronic medical record system and clinical trial management system. No future uses are envisioned.

### **Procedures during treatment**

As dictated by standard of care or a clinical trial.

### **Tumor Assessments**

To be done approximately every 8 weeks.

### **Follow-up Procedures**

Patients will be followed every 3 months ( $\pm$  1 month) until death. Follow-up will consist of survival contacts via medical record review, telephone call, or review of the Social Security Index.

### **Removal of Subjects from Study**

Patients can be taken off the study at any time at their own request, or they may be withdrawn at the discretion of the investigator for behavioral or administrative reasons. The reason(s) for discontinuation will be documented and may include:

- **Patient withdraws consent;**
- **Patient is unable to comply with protocol requirements;**
- **Treating physician judges continuation on the study would not be in the patient's best interest.**

## **5.0 Measurement of Effect**

---

### **Feasibility**

This feasibility study is an evaluation and analysis of the potential of a proposed methodology that is based upon molecular profiling to support decision making in individualized cancer therapy for patients with incurable malignancies. Like other feasibility studies, we will objectively and rationally uncover the strengths and weaknesses of this approach in the academic environment of UCSD with our collaborators. This feasibility study will evaluate this methodology's potential for success. We termed this a feasibility study because genomically driven trials, especially in this setting, are relatively new. As such, we might encounter logistical hurdles that will need to be addressed and overcome before a definitive trial is performed.

For the primary objective, we consider matching therapy for  $\geq 40\%$  of patients ( $N \geq 30$ ) in each Group to define a successful feasibility endpoint. Additional measure of feasibility will be the ability to enroll patients in each Group, the turnaround time for genomic analysis, and the ability to identify actionable genomic alterations.

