The current study will perform tumor molecular profiling through FoundationOne™ to navigate patients to a matched therapy at the discretion of their treating physician. For those patients with an actionable tumor alteration, matched therapy will be recommended by the Study Committee (or Molecular Tumor Board) from either FDA approved drugs or matched agents under investigation in a separate clinical trial. Those patients, for whom there are no available matched treatments, will serve as the unmatched therapy controls.

Patients with no actionable alterations by FoundationOne™ will be considered to have completed their participation in the study. Their basic data will be captured including demographics and tumor type and accounted into the denominator for feasibility analysis.

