### Molecular Matching and Molecular Tumor Board/Study Committee

FoundationOne™ results of patients who have genomic alterations detected will be provided to the Molecular Tumor Board, which consists of the study principal investigators, co-investigators, the treating medical oncologist, other medical oncologists, surgical oncologists, radiologist, pathologist, other physicians, scientist specializing in genomics, a genetic counselor, and basic/translational scientists.[9] Since timeliness is essential for managing patients enrolled in this study, a Study Committee, that includes, but is not limited to, the study principal investigators and the treating medical oncologist may provide recommendations on an as needed basis between Molecular Tumor Board meetings in order to avoid delaying treatment. Using the aforementioned molecular aberrations, which represent druggable targets, either through direct pathway inhibition or through an associated pathway (via “crosstalk”), the “molecular individuality” of these tumors will be approached via a customized strategy.[9] Using an “N-of-One” model of precision medicine, the independent Study Committee will make a recommendation for a matched therapy that consists of at least one drug that targets a molecular alteration. Actionability will be limited by our ability to obtain drug(s). We expect 50-70% of patients will have potentially actionable alterations. This percentage is increasing rapidly as we learn more about the pathways and the drugs. We anticipate approximately 40% of patients with actionable alterations will be able to receive molecularly targeted “matched” treatment. These patients will be considered ARM A in each group. Expert opinion, rather than a preconceived algorithm will determine a molecularly matched therapy because a preconceived algorithm [6, 10] will likely be out of date by the time the trial ends. We realize there are downsides to “expert” opinion. However, as a feasibility trial,

we feel that it is a reasonable way to address this issue, and mimics what is done in the community.

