## **6.2 Sample Size and Accrual**

This is a feasibility study with descriptive analysis as the primary analysis to characterize the study findings. We plan to enroll a total of 150 patients in Groups 1 and 2 and an unlimited number of patients in Group 3 (of up to 1000 patients) with their blood/tissues subject to the FoundationOne™ assay. We project to enroll patients in 30 months plus additional 6 months of follow-up. The total study period is 3 years. We expect that the accrual rate is 2 patients per month for Groups 1 and 2, and 4 patients per month for Group 3 in the first year. After the study mechanism is established and if we begin to see objective responses with matched therapy, we expect these rates to increase to 3 patients per months for Groups 1 and 2, and 5 patients per month for Group 3 in subsequent years. The total and percent of patients in Arm A and Arm B for each group will be determined to assess the feasibility of this study. With the comprehensive genomic profiling, we expect that 40% of the patients (N=30) will be in Arm A and 60% of the patients (N=45) will be in Arm B for all three patients groups.

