## **6.4 Sample Size Calculation**

All exploratory analysis will test the hypothesis of greater response rate in Arm A than that in Arm B. With an estimated sample size of 30 (ARM A) and 45 (ARM B) in each group, we can estimate the response rate with a standard error no larger than 0.09 and 0.07, respectively. We will have sufficient statistical power to detect the difference between groups only if the difference between groups is sufficiently large. For example, with the sample size of 30 and 45 for Arm A and Arm B, we will have 79% power to detect the response rate of 0.25 and 0.05 between the two arms with one-sided 10% type I error rate using the continuity corrected chi-square test.

We will have more than 80% power to detect the difference between Arm A and Arm B using the log-rank test when the median PFS is 4 months and 2 months for the two arms, respectively.

In addition, in Group 1A, we will estimate the proportion of patients who are initially unresectable (as deemed by two surgeons) but converted to resectable (as deemed by two surgeons) after 8 weeks of the matched treatment, or if ever resected. With 30 patients, we expect to see at least one patient becomes resectable with a probability of 0.79, 0.96, and 0.99 if the conversion rate is 0.05, 0.10, and 0.15, respectively. We expect to see at least 2 patients become resectable with a probability of 0.82 and 0.95 if the conversion rate is 0.10 and 0.15, respectively. One-sided nominal level at 10% will be used to declare statistical significance. No P value adjustment for multiplicity will be applied due to the exploratory nature of the study. All study results need to be confirmed by future studies with larger sample sizes.

- The response rate (proportion of patients reaches CR or PR) will be estimated based on RECIST for each patient group and each treatment arm.
- The tumor regression rate (in %) will be calculated by the percent tumor size reduction from baseline to after treatment will be determined in and across patient groups.
- Progression-free survival (PFS) and overall survival (OS) will be determined in and across patient groups and treatment arms.

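### The 40% (30 of 75) matched-therapy target and Arm A size contradict the protocol's own expected yield of 20-28% of profiled patients

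*Protocol*

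**What the plan says.** Two expectations for the matched share stand side by side in the Protocol.

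- **Section 3.2, Molecular Matching and Molecular Tumor Board/Study Committee:** "We expect 50-70% of patients will have potentially actionable alterations", and then "We anticipate approximately 40% of patients with actionable alterations will be able to receive molecularly targeted" matched treatment. These matched patients form Arm A.
- **Section 6.2, repeated in Section 6.4:** "we expect that 40% of the patients (N=30) will be in Arm A and 60% of the patients (N=45) will be in Arm B". Every group is given this same split.

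Section 5.1 (Feasibility) turns the second figure into the success rule. At least 40% of patients, with N at least 30, must be matched "in each Group to define a successful feasibility endpoint".

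On the denominator, Section 1.2 says that patients without an actionable alteration have finished their participation. Their basic data are nevertheless "accounted into the denominator for feasibility analysis".

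On enrolment, Section 6.2 plans "a total of 150 patients in Groups 1 and 2 and an unlimited number of patients in Group 3 (of up to 1000 patients").

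Sections 6.4 and 6.6 build on 30 and 45 patients per group. They give standard errors of at most 0.09 and 0.07. They say "we will have 79% power to detect the response rate of 0.25 and 0.05 between the two arms" at a one-sided 10% level with the continuity-corrected chi-square test. They also give a 0.79 probability of at least one resection in Group 1A at a 5% conversion rate.

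**The concern.** The same 40% is applied to two different populations: patients with an actionable alteration in Section 3.2, and all patients in Sections 5.1, 6.2 and 6.4. Section 5.1 cannot be rescued by reading its 40% as a share of actionable patients. Section 1.2 puts the non-actionable patients in the denominator, and 30 is 40% of 75, which is a whole group (30 + 45).

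Section 5.1 is the only numerical success rule for the primary endpoint. If enrolment and matching go as Section 3.2 expects, that rule is almost certain not to be met. The precision and power quoted for Groups 1 and 2 would also rest on an Arm A that those groups are not expected to have.

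**Working it through.** **Inputs.** Actionable share 50-70% and matched share of those 40% (Section 3.2). Threshold 40% and 30 per Group (Section 5.1). Arms 30 and 45, 150 patients in Groups 1 and 2 together, and Group 3 accrual of 4 per month in the first year then 5 per month over 30 months in all (Section 6.2). Response rates 0.25 and 0.05, one-sided 0.10 (Section 6.4). Assumption: Groups 1 and 2 have 75 patients each. The protocol gives only the total of 150, but 30 + 45 = 75 supports an even split.

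**Step 1. The plan's own figures reproduce.** With n1 = 30 and n2 = 45, the pooled rate is (30 × 0.25 + 45 × 0.05)/75 = 0.13.

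- Null SE = √(0.13 × 0.87 × (1/30 + 1/45)) = 0.0793
- Alternative SE = √(0.25 × 0.75/30 + 0.05 × 0.95/45) = 0.0855
- Continuity correction = 0.5 × (1/30 + 1/45) = 0.0278
- Power = Φ[(0.20 − 0.0278 − 1.2816 × 0.0793)/0.0855] = Φ(0.83) = 79.6%, against the stated 79%
- P(at least one resection at 5%) = 1 − 0.95^30 = 0.785, against the stated 0.79
- Maximum Arm A SE = √(0.25/30) = 0.091, against the stated 0.09

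So the calculations are right for 30 and 45. The question is whether those sizes follow from the plan.

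**Step 2. Implied yield.** 0.50 × 0.40 = 20%, and 0.70 × 0.40 = 28%. Arm A per 75 patients is 75 × 0.20 = 15 to 75 × 0.28 = 21.

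**Step 3. Chance of meeting Section 5.1 in Group 1 or Group 2.** The binomial tail P(X ≥ 30), n = 75, is:

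| True matched rate | P(at least 30 of 75) |
|---|---|
| 20% | 0.00006 |
| 24% | 0.0015 |
| 28% | 0.017 |
| 40% | 0.54 |

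**Step 4. Group 3.** Projected accrual is 12 × 4 + 18 × 5 = 138. Expected Arm A is 138 × 0.20 = 28 to 138 × 0.28 = 39. P(at least 30) is 0.34 at 20% and 0.96 at 28%. P(at least 40%) is below 0.001 at either rate. At 1000 patients Arm A would be 200-280, and the 40% limb would still be missed.

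**Step 5. Response power in Groups 1 and 2.** The Step 1 formula is used at the implied sizes. If non-actionable patients are outside Arm B, Arm B is 75 × 0.50 × 0.60 = 22.5 to 75 × 0.70 × 0.60 = 31.5, taken as 22 and 32. If every unmatched patient is in Arm B, it is 60 or 54.

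| Arm B definition | Arms A/B | Power |
|---|---|---|
| Non-actionable excluded | 15/22 | 49.7% |
| Non-actionable excluded | 21/32 | 65.2% |
| All unmatched included | 15/60 | 67.6% |
| All unmatched included | 21/54 | 74.6% |

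**Step 6. Other figures for Arm A of 15-21.**

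- Maximum SE: √(0.25/21) = 0.11 to √(0.25/15) = 0.13, against 0.09
- P(at least one resection at 5%): 1 − 0.95^15 = 0.54 to 1 − 0.95^21 = 0.66, against 0.79

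**Step 7. Log-rank check.** Medians of 4 and 2 months give a hazard ratio of 0.5. With Schoenfeld's formula, one-sided 0.10 and an event in every patient, power is 95% at 30/45. At the four implied pairs, in the order of the Step 5 table, it is 78%, 88%, 87% and 92%.

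**The case against.** Several stronger conclusions are tempting, and the document does not support them.

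- **That 20-28% is the true expectation and 40% the mistake.** Sections 6.2 and 6.4 are also the investigators' stated view, and Section 3.2 says the actionable share is rising. What is shown is two expectations that cannot both hold. The rising share does not reconcile them: even with every patient actionable, 1.00 × 0.40 only just reaches 40%.
- **That the study would be declared infeasible.** Section 5.1 names further feasibility measures, Sections 6.2, 6.3 and 6.5 call the primary analysis descriptive, and no action follows from missing 40%. Missing it means that the defined success endpoint is not met, and no more.
- **That Arms A and B together hold far fewer than 75.** This is one reading. Section 6.6 limits Arm B to patients without an available drug or coverage, and Section 1.2 ends participation for the non-actionable. But the Study Summary gives the same reasons for Groups 1 and 2 only as examples, and Section 6.1 places anyone given physician's-choice chemotherapy in Arm B. Section 3.2 gives non-actionable patients that treatment, and the 40%/60% split leaves no third category. Both readings are therefore shown.
- **That the PFS power claim fails.** The protocol claims more than 80%. Three of the four scenarios exceed that and the fourth gives 78%, so the claim largely holds.
- **That Group 3 is underpowered.** Its size is not fixed at 75. At 138 patients response power is about 76-93%, depending on the matched rate and the Arm B definition, and N at least 30 is met or nearly met in expectation. Only the 40% limb fails.

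It is also fair to say that a feasibility bar may be set above expectation on purpose, and that the power statements are exploratory. Neither point removes the need for the threshold and the expected rate to refer to the same patients.

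**Conclusion.** The contradiction between Section 3.2 and Sections 5.1, 6.2 and 6.4 stands and should be corrected. On the Section 3.2 rates, Groups 1 and 2 each have at most a 1.7% chance of meeting the success rule, and Group 3 less than 0.1% of meeting its 40% limb. For Groups 1 and 2, the stated response power, Arm A standard error and Group 1A resection probability are all more favourable than those rates allow.

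The Group 1 and 2 figures assume 75 patients each. The size of the power loss also depends on an Arm B definition that the protocol leaves unclear. The Group 3 figure uses the projected 138 patients, but the conclusion on the 40% limb is the same at 1000. The finding does not extend to the log-rank power or to Group 3 power.

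**What to change.** 1. Reconcile Sections 3.2, 5.1, 6.2 and 6.4 to one denominator and one expected matched rate.
2. Report the primary proportion over all profiled patients, with its 95% confidence interval.
3. If Section 3.2 stands, either apply the 40% only to patients with an actionable alteration, or restate the threshold on the all-patient scale. In either case give the probability of passing at the expected rate. How demanding the bar should be is the sponsor's choice.
4. State whether patients without an actionable alteration count in Arm B, and align the Study Summary and Sections 1.2, 3.2, 6.1 and 6.6.
5. In Sections 6.2, 6.4 and 6.6, restate the response power, standard errors and resection probabilities for Groups 1 and 2 at the implied arm sizes, and treat Group 3 separately.

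The cost is protocol wording, with less favourable power and precision on paper. Keeping an expected 30 in Arm A instead would need about 30/0.28 = 107 to 30/0.20 = 150 profiled patients in each of Groups 1 and 2, rather than 75.
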